## Abstract

**Introduction:**

Increasing numbers of children require having all, or part, of their nutritional intake via gastrostomy. More parents are using home-blended meals to feed their children, with many reporting beneficial effects such as improved gastro-oesophageal reflux, less constipation and less distress in their child.

This study aims to identify the important outcomes of tube feeding in this population, compare the safety, outcomes and resource use of those on a home-blended diet compared with a formula diet and assess feasibility of long-term follow-up of children recruited to this study.

**Methods and analyses:**

This is a mixed methods study of children (aged 6 months to 18 years) who are gastrostomy feed dependent recruited via general, community and specialist paediatric and dietetic services.

*Workstream*
*1* (*WS1*): a qualitative study involving semistructured interviews with parents (n~20) and young people (n~5–10), and focus groups with health professionals (n~25), will provide evidence of appropriate outcome measures and the feasibility/acceptability of proposed data collection methods for WS2. It will gather data on: desired outcomes of gastrostomy feeding, variability in diets and reasons; use of oral feeding; perceived benefits of the alternative diets, resources associated with gastrostomy feeding and safety issues. Data will be analysed using thematic analysis.

*WS2*: a cohort study of 300 children who are gastrostomy fed. Data will be collected at months 0, 9 and 18 from parents, children (if appropriate) and clinicians using standardised measures and questionnaires developed specifically for the study. Data collected will include gastrointestinal symptoms, health and other outcomes (child, parent), dietary intake, anthropometry, healthcare usage, safety outcomes and resource use. Outcomes in the home-blended and formula groups will be compared using appropriate multiple regression analyses.

**Ethics and dissemination:**

The study has been approved by a research ethics committee (REC reference: 19/YH/0028). Results will be disseminated through publications and presentations for professionals and families.

**Study registration number:**

ISRCTN13977361.

Strengths and limitations of this studyA multicentre study of a large number of children who are gastrostomy fed.Key outcomes will be determined from qualitative work with parents, young people and professionals.The study will use validated measures for gastrointestinal symptoms, nutritional intake, health and other outcomes, and quality of life data collection.This is an observational study with no randomisation, therefore confounding and bias may be of concern.

## Introduction

There are growing numbers of children with complex health conditions who are dependent on medical technologies to maintain their health, and gastrostomy (or enteral) feeding is one such technology. The authors’ own analyses of inpatient hospital (Hospital Episodes Statistics, HES) data found that among children with life-limiting conditions (LLC)^1^ in England, the number having permanent gastrostomy surgery each year has risen from 183 in 2000/2001 to 1004 in 2014/2015. In 2014/2015, the total number of children with an LLC, aged 0–19 in England, who have ever had a gastrostomy was 10 154. This is much higher than published estimates of ~430 children.^2^

Children requiring some or all of their nutrition via gastrostomy tubes have a wide range of underlying diagnoses, including neurodisability, inherited metabolic diseases, congenital cardiac conditions, cystic fibrosis, gastrointestinal diseases and cancer.

At present, in the UK, the recommended feed for children on enteral feeding is commercially produced complete liquid nutrition (formula), prescribed by the child’s dietitian.^3^ However, there is a growing body of parents who are interested in and/or choosing to feed their children meals they have prepared themselves which are then liquidised so they can be administered via a gastrostomy (referred to forthwith as ‘home-blended foods’).^4–6^ Parents choosing to use home-blended foods have reported benefits such as improved gastro-oesophageal reflux, less constipation and less distress in their child.^7^ There are also perceived psychosocial benefits: it may fulfil parents’ need to nurture, and the child is not excluded from sharing the same food as the rest of the family. Prescribed formula, in contrast, is regarded as a medical product rather than food.^6^

Limited research evidence^8^ and reports from clinicians suggest that the long-term use of gastrostomy feeds for children with complex health conditions can result in complications including progressive feed intolerance/gut failure.^8^ There are suggestions that a home-blended diet may reduce the risk of gut failure but there is currently no evidence to support this.

Recent national surveys of paediatric dietitians in the UK^4^ and the USA^5^ both found that more than half of respondents would recommend the use of a home-blended diet (56% and 58%, respectively). In the UK, however, that recommendation was to use home-blended food as a supplement to formula feeds rather than their exclusive use.

At the same time, concerns have been raised by professional organisations, including the European Society for Paediatric Gastroenterology Hepatology and Nutrition and British Dietetic Association, about the risks associated with a diet of home-blended foods. These include: nutritional inadequacy, microbial contamination and blockage of the gastrostomy tube. Policy/position statements from such organisations do not recommend that children (or adults) are fed home-blended foods through their gastrostomy tubes.^9^ Importantly, it was acknowledged in these guidelines that the evidence for this statement is low and further research is likely to have an impact on this recommendation.

## Methods and analyses

The research question is: What are the risks, benefits and resource implications for using home-blended food for children with gastrostomy tubes compared with currently recommended formula feeds?

The objectives are:

To identify the important outcomes of gastrostomy feeding for parents, young people and health professionals.To assess the safety of home-blended diets for children who are gastrostomy fed compared with liquid formula diets.To identify and quantify the benefits of home-blended diets compared with liquid formula feeds for children who are gastrostomy fed and their parents.To identify and quantify the resources (family and statutory services) required to support home-blended diets compared with formula feeds.To assess whether long-term follow-up of children who are gastrostomy fed is feasible using routine data sources.

This study will use a mixed methods exploratory sequential design^10^ with two workstreams (WS), with findings from WS1 informing the design and methods for WS2. The research team comprises clinical and methodological experts including applied social scientists (leading WS1) and a clinical epidemiologist leading WS2.

### Workstream 1

#### Design

Phenomenological qualitative research with young people, parents and healthcare professionals. Interviews (young people, parents) and focus groups (healthcare professionals) will be used to investigate views on a number of topics relevant to informing final decisions regarding the design of the cohort study in WS2 as well as generating ‘stand-alone’ evidence on young people’s, parents’ and professionals’ views about gastrostomy feeding and the use of home-blended diets.

#### Eligibility criteria

Parents (n=20) of children and young people (aged 6 months to 18 years inclusive) who are fed via a gastrostomy.Young people (n=5–10) aged 12–18 years currently using a gastrostomy and with no significant cognitive impairments.Health professionals who provide or support the nutritional care of children with a gastrostomy, specifically paediatricians (n=6–8), dietitians (n=6–8), children’s community nurses (n=6–8) and speech and language therapists (n=6–8).

#### Sampling

Purposeful sampling will be used. Parents will be sampled to ensure representation of different diets (formula vs home blended vs mixed), dietary history (ie, unchanged since gastrostomy vs change of diet), range of children’s ages, duration of gastrostomy feeding and broad stance of clinicians overseeing child’s care regarding home-blended diets (ie, supportive vs unsupportive). Healthcare professionals will be sampled to ensure representation of the range of healthcare professions (eg, paediatricians, dieticians) who support children who are gastrostomy fed, stance on home-blended diets and experience of supporting children using home-blended diets.

#### Recruitment

We will recruit via general, community and/or specialist paediatric services in English National Health Service (NHS) Trusts and children’s nutrition and dietetic services attached to, or working into, these services. Services will be selected to represent the broad range of stances regarding home-blended diets (supportive, neutral and unsupportive). Based on estimated numbers of children using a home-blended diet we plan to recruit from six NHS Trusts in WS1.

For parents and young people, research staff/clinicians will identify eligible participants and provide the study team with an anonymised list, detailing sampling characteristics. The study team will select which participants to approach based on sampling criteria (see the Eligibility Criteria section). The site research staff/clinicians will then approach the selected participants in clinic or via post. Parents and young people who return response forms will be contacted by the study team and an interview time and date will be arranged.

#### Data collection

Individual interviews (young people, parents) and focus groups (professionals) will be used to collect data. Parents will be offered the choice of telephone or face-to-face interview. Consent will be recorded at the start of the interview/focus group. For young people aged 12–15 years, child assent and parent consent will be obtained.

Interview/focus group schedules will cover the following topics (tailored to the characteristics of the interviewee(s)):

Typical diet followed and factors which may affect adherence to that diet.In terms of blended diets, factors influencing decision to use diet, types of food comprising diet, parental management of diet, support and guidance offered and adherence to guidance.Desired and observed immediate and longer term health and quality of life (QoL) outcomes (including unanticipated and/or undesirable) for the child of gastrostomy feeding and perceived impacts of the type of diet used.Observed symptoms associated with gastrostomy feeding (eg, reflux, constipation) and impacts of type of diet on symptoms.Perceived outcomes for parents of their child being fed by gastrostomy, and impacts of type of diet on these outcomes.Perceived/experienced risks/safety issues and other drawbacks associated with gastrostomy feeding, including the type of diet used.Reported/perceived costs to families and the NHS (financial, time) of using gastrostomies and the impact of type of diet on those costs.

In addition, interviews with parents will explore views regarding feasibility and acceptability (in terms of parent participation) of the proposed design of the cohort study (eg, proposed recruitment methods, collecting nutritional data, respondent burden and retention strategies).

For interviews with young people who have communication impairments, we will use their preferred communication systems and, if necessary, use or create visual tools (eg, Talking Mats^11^) to facilitate the interview.^12^

With participants’ permission, interviews/focus groups will be audio recorded and verbatim transcripts obtained.

#### Data analysis

An inductive approach to data analysis using thematic analysis techniques^13^ will be used to identify and describe experiences of gastrostomy feeding, ways in which blended-food diets are being implemented, outcomes that are important across the sample, resource implications and complications associated with blended feeds, and to examine the acceptability and appropriateness of piloted measurement tools.

Specifically, we will use the Framework approach^14^ to facilitate systematic data management and ensure audit trails of the data management process:

Researchers familiarise themselves with the data, and identify themes and key issues.Based on identified themes and any a priori issues (eg, acceptability of proposed WS2 data collection tools, outcomes associated with gastrostomy feeding, resource use), an index of themes is constructed (the thematic framework).Data are then indexed according to which theme(s) in the analytical framework they relate to. The indexed data from each case (eg, participant, focus group) are summarised onto a series of thematic matrices (or charts). Each chart is divided into columns, allowing relevant data to be organised according to subthemes/issues. A single row on each chart holds one participant’s data. Thus, reading along a row provides an overview of everything an individual spoke about in terms of a specific issue. Reading down the chart (or down a column) allows comparison between participants’.The final stage of analysis involves ‘reading’ of the charts, composing ‘analytical notes’ which describe the data and developing interpretation and hypotheses which are then tested against the charts and raw data. To start, data will be analysed by participant group after which there will be a process of comparison between groups.

#### Integrating WS1 findings into final decision-making regarding WS2

WS1 findings will be presented to an expert study steering committee (SSC) comprising parent, clinical and academic expertise. The SSC will be tasked, in discussion with the research team, with agreeing which outcomes to measure in WS2 and selecting appropriate measurement/data collection tools for these in terms of feasibility (eg, respondent burden) and comprehensiveness. Where additional outcome domains not included in the original protocol are identified in WS1, candidate outcome measures will be identified by the research team and presented to the SSC. The SSC will also review WS1 findings regarding the need to include further descriptive and predictor variables for WS2, and the team’s proposed means of collecting data on these.

### Workstream 2

#### Design

A prospective cohort study with an initial 18-month follow-up period but also including an assessment of the potential for long-term (10 years+) follow-up using routine data sources to measure key outcomes for these children.

#### Eligibility criteria

Children (aged 6 months to 18 years inclusive) who receive most or all of their nutrition via gastrostomy tube. Parents of participating children will also take part in the study. We are including child and parent dyads in order to measure child and parent outcomes (eg, QoL); therefore, children who do not live with a biological or adoptive parent are not eligible to take part. The study is limited to families who reside in England (see table 1 for summary of inclusion and exclusion criteria).

**Table 1 T1:** Eligibility criteria

	Eligible	Ineligible
A	Child is at least 6 months old and under 19 years.	Infants up to 6 months and young people who are 19 years and older.
B	Child is gastrostomy feed dependent.	Child has another type of feeding tube (eg, nasogastric, jejunostomy).
C	Child receives most or all of their nutrition via the gastrostomy.	
D	Child is living with parent(s): biological or adoptive.	Child is not living with a parent (eg, in residential setting or foster care).
E	Family resident in England.	Family not resident in England.

#### Sample size

Given that no data are available on the exact proportion of children who receive formula feeds versus a home-blended diet in England, various scenarios were explored to ensure that the study would be adequately powered. A sample size of 300 for the analysis (assuming there are twice as many formula fed as home blended) should enable us to estimate proportions within each group to within a margin of error of ≤10% and continuous measures (eg, Pediatric Quality of Life Inventory (PedsQL) assuming SD 20) to within an SE of 4 points.

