#### Assessing safety (objective 2) and benefits (objective 3)

The safety and benefits of blended diet compared with formula diet will be assessed using multivariable regression analyses. The type of regression will depend on the outcome of interest: logistic (tube blockage, appropriate nutritional content; yes/no), linear (PedsQL gastrointestinal module score, BMI SDS or upper arm circumference, calories, Parenting Moral Index (PMI), EQ-5D), Poisson or negative binomial (number of A&E or hospital admissions for infections or complications of gastrostomy tube). Each analysis will account for the multiple confounding factors in this population (age, underlying diagnoses, comorbidities, outpatient attendance, parental factors, socioeconomic status) and the main covariate of interest will be feeding status (blended vs formula). Study site will be added as a random effect to the models to allow for site-level variation. Estimates and 95% CIs will be reported from the regression model for each outcome measure.

The flow of participants through the study will be detailed including the number of individuals contributing to each analysis. The amount of missing data will be summarised for each outcome measure and multiple imputation will be used to assess the robustness of the results. Results will be compared with the complete case analyses and important differences discussed. Sensitivity analyses will be considered to explore departures from the missing at random assumption.

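### The stated SE of 4 points for continuous measures does not follow from the protocol's inputs: it is evidently a 95% half-width for the blended group (SE 2.0), and neither precision figure describes the between-diet comparison

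*Protocol article*

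**What the plan says.** The protocol article sizes Workstream 2 by precision. Its Sample size section reports that "various scenarios were explored to ensure that the study would be adequately powered". It then takes "A sample size of 300 for the analysis", "assuming there are twice as many formula fed as home blended", and draws two conclusions. The study should be able to "estimate proportions within each group to within a margin of error of ≤10" per cent, and it should estimate continuous measures such as the PedsQL, "assuming SD 20) to within an SE of 4 points".

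The section gives no alpha, power, target difference, or precision for a difference between the diets. Objectives 2, 3 and 4 each set home-blended against formula feeding. The section on assessing safety and benefits makes feeding status the covariate of main interest and states that "Estimates and 95% CIs will be reported from the regression model for each outcome measure". The abstract describes Workstream 2 as "a cohort study of 300 children who are gastrostomy fed", with data at 0, 9 and 18 months.

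**The concern.** An SE is fixed by the SD and the number of children, and the section gives both. With an SD of 20, an SE of 4 corresponds to 25 children, but the smaller group is meant to hold 100. The two precision claims in the same sentence therefore cannot both be tight statements about one sample, and one of them looks mislabelled.

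The second problem is what the figures describe. A claim about power is followed only by the precision of estimates within a single group. A reader who wants to know how finely the study can separate the two diets will either double the literal SE or take 4 points as the study's resolution. Neither gives the right answer.

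**Working it through.** **Inputs.** From the Sample size section: 300 analysed, 2:1 formula to blended (200 and 100), SD 20. The 95% level is stated for the regression estimates; I assume it also underlies the margin of error. For proportions I take the worst case, p = 0.5.

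**Step 1: the proportion figure.** The half-width is 1.96 × √(0.25/n).
- Blended, n = 100: 1.96 × 0.05 = 9.8%.
- Formula, n = 200: 1.96 × 0.0354 = 6.9%.

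The ≤10% statement reproduces in both groups and is tight in the smaller one.

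**Step 2: the continuous figure, read as an SE.**
- Blended: 20/√100 = 2.00.
- Formula: 20/√200 = 1.41.
- Whole cohort: 20/√300 = 1.15.
- Difference between diets: 20 × √(1/100 + 1/200) = 2.45.

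None of these is 4.

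**Step 3: what does give 4.** The 95% half-width in the blended group is 1.96 × 2.00 = 3.92 (3.97 with the t quantile on 99 degrees of freedom). The sample size behind each claim also agrees:
- for a half-width of 4 points, (1.96 × 20/4)² = 96.04;
- for a half-width of 10%, (1.96 × 0.5/0.10)² = 96.04.

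The two statements match exactly once the 4 is a 95% half-width.

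The alternatives fail. An SE of 4 needs (20/4)² = 25 children, where the proportion margin would be 1.96 × √(0.25/25) = 19.6%. A design effect of 4 would raise the blended SE to 2.00 × √4 = 4.0, but none is stated, and it too would double the margin to 19.6%.

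**Step 4: size of the mislabelling.** A literal reader computes 1.96 × 4 = ±7.8 points. The inputs give ±3.9 in the blended group and 1.96 × 1.41 = ±2.8 in the formula group.

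**Step 5: the comparison.** At 200 and 100, unadjusted and before site effects:
- means: SE 2.45, half-width 1.96 × 2.45 = ±4.8 points;
- proportions at p = 0.5: 1.96 × √(0.25/100 + 0.25/200) = ±12.0 percentage points;
- detectable difference, assuming two-sided 5% alpha and 80% power: (1.96 + 0.84) × 2.45 = 6.9 points. On the same alpha, power for a true 4-point difference is about 37%.

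**Step 6: dependence on 300 being analysed.** For illustration only, with an assumed 80% retention (160 and 80):
- blended margin: 1.96 × √(0.25/80) = 11.0%;
- mean difference: 1.96 × 20 × √(1/80 + 1/160) = ±5.4 points;
- difference in proportions: 1.96 × √(0.25/80 + 0.25/160) = ±13.4 percentage points.

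The documents give no retention figure.

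**The case against.** The strongest reply is that being within an SE of 4 is an upper bound, which 2.0 satisfies, so nothing false has been said and the slip is conservative. The direction is right: the text understates per-group precision and does not make 300 too small for the per-group aim. But a bound at twice the true value, next to a margin that is tight at 9.8%, is not what the section can have meant, and it will be misread.

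It can also be said that an observational cohort may properly be sized by precision, that a condensed article need not show every scenario, and that an analysis plan is promised. All of that stands. What remains is narrower: the section makes a power claim and then supports it with figures for a different quantity.

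Some stronger readings are tempting and are not supported:
- **That the comparison is less precise than the figures stated.** This holds for proportions (12.0 against 10) and for means once the 4 is read as a half-width (4.8 against 3.9). It fails against a literal SE of 4, because the SE of the difference is 2.45.
- **That the mislabelled figure would make a null safety result look reassuring.** The listed safety outcomes are blockages, infections, and admissions or attendances, modelled by logistic or count regression. The SD-20 figure does not describe them.
- **That the whole study is a diet comparison.** Objectives 1 and 5 are not comparative.
- **That almost any loss breaks the ≤10% margin.** This is so only near p = 0.5, where 97 blended children are needed. At p = 0.2, 62 suffice (3.84 × 0.16/0.01 = 61.5), and at p = 0.1, 35 (3.84 × 0.09/0.01 = 34.6). Baseline estimates also suffer no follow-up loss, and reminders, vouchers and multiple imputation are planned.
- **That a smaller blended share or clustering by site defeats the design.** Such scenarios rest on figures that the documents do not give.

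**Conclusion.** The concern holds as a labelling error with a secondary gap. On the protocol's own inputs the SE is 2.0 in the blended group and 1.4 in the formula group. No natural reading yields 4, and the 95% half-width of 3.9 in the blended group explains it on the same basis as the proportion margin. That conclusion needs only the stated sample size, split and SD, plus the 95% level.

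The gap is that adequate power is claimed for a study whose objectives 2 to 4 compare diets, while both figures given are within-group. The comparison figures of ±4.8 points and ±12 percentage points are unadjusted. Confounder adjustment, the site random effect or a more unequal split would change them: at 50 and 250, for example, the SE of the difference would be 3.10. The 6.9 points also rests on an alpha and power that the protocol does not state.

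The article is also loose on whether 300 is the number enrolled or the number analysed, which matters because the precision applies to the latter. The weight is minor to moderate: no sample size, analysis or estimate changes, and the ≤10% figure is correct at 200 and 100.

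**What to change.** 1. In the Sample size section, replace "to within an SE of 4 points" with: *to within a 95% margin of error of about 4 points (SE 2.0) in the home-blended group and 2.8 points (SE 1.4) in the formula group*.
2. Replace the power claim in "various scenarios were explored to ensure that the study would be adequately powered" with a precision statement for the comparison, marked as unadjusted and before site effects: *with 300 analysed, the difference between diets has an SE of 2.45 and a 95% half-width of about 4.8 points for means (SD 20), and a 95% half-width of about 12 percentage points for proportions at p = 0.5*.
3. If a detectable difference is quoted (6.9 points), label it as assuming two-sided 5% alpha and 80% power.
4. State that the figures apply to 300 children analysed and widen with loss to follow-up, and reconcile this with the abstract's cohort of 300. Mark any retention, blended-share or intracluster-correlation scenario as illustrative.

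This costs wording only, with no added recruitment. The per-group continuous precision becomes more favourable than the literal text. The comparison, now without a figure, gains one.
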